# Randomized, open-label, multicenter study of azithromycin compared with doxycycline for treating anorectal *Chlamydia trachomatis* infection concomitant to a vaginal infection (CHLAZIDOXY study)

**DOI:** 10.1097/MD.0000000000014572

**Published:** 2019-02-15

**Keywords:** anorectal infection, azithromycin, *chlamydia trachomatis*, doxycycline, women

## Abstract

**Background::**

*Chlamydia trachomatis* can lead to a persistent infection in the lower gastrointestinal tract, suggesting a potential role of autoinoculation of cervical chlamydial infection from the rectal site, contributing to repeat infections. Moreover, around 75% of women with urogenital *C. trachomatis* have concurrent anorectal infection. Current treatment guidelines for urogenital *C. trachomatis* infection recommend either a single 1 g dose of azithromycin or doxycycline 100 mg twice daily for 7 days. Doxycycline appears to be more effective in treating anorectal infections as suggested in a population of men who have sex with men, but no randomized controlled trial (RCT) had directly compared azithromycin with doxycycline for the treatment of rectal infections. We propose an open-label RCT to compare the microbial cure obtained with a single 1 g dose of azithromycin versus 100 mg of doxycycline twice daily for 7 days, for the treatment of anorectal *C. trachomatis* infection concurrent to urogenital infection in women.

**Methods and study design::**

A total of 460 women with *C. trachomatis* urogenital infection will be enrolled in the study. Women will be asked to provide self-collected anorectal swabs and will be randomized to receive either a 1 g single dose of azithromycin or doxycycline 100 mg twice daily for 7 days. Clinical and biological data will be collected and patients will complete questionnaires about their sexual behavior. The primary outcome is the microbial cure rate, defined as a *C. trachomatis* negative nucleic acid amplification test (NAAT) result in the anorectal specimens 6 weeks after treatment initiation among women with a *C. trachomatis* positive urogenital and anorectal NAAT result at the baseline. The secondary outcome is autoinoculation from the rectum to the vagina, which will be evaluated based on the number of women with the same *C. trachomatis* genotype profile that will be identified in an anorectal-positive specimen obtained 6 weeks after treatment initiation and in a vaginal-positive specimen obtained four months after treatment.

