Adequate treatment for anorectal *C. trachomatis* is currently under debate. A recent meta-analysis found a pooled treatment efficacy of 82.9% for a single 1 g dose of azithromycin and 99.6% for 100 mg of doxycycline twice daily for 7 days.^[20]^ While this suggests that doxycycline may be a more effective treatment, it must be emphasized that the quality of the evidence was poor, as the meta-analysis was based entirely on observational studies, with 75% (6/8) of the studies being retrospective case note reviews. If rectal *C. trachomatis* is a hidden reservoir influencing transmission rates and considering the potential complications of cervical infections, providing further evidence of the need for effective rectal treatments among women is highly relevant. These circumstances highlight the need for RCT evidence comparing azithromycin with doxycycline for the treatment of anorectal *C. trachomatis* in women. Our hypothesis is that the efficacy of azithromycin for anorectal *C. trachomatis* infection may be lower than that of doxycycline, resulting in reinfection by autoinoculation from the rectum to the vagina.

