#### Follow-up at 6 weeks

2.5.4

All women will be asked to attend the participating center 6 weeks after treatment initiation.

During this visit, the research nurse will look at the *C. trachomatis* detection result of the anorectal swab performed at baseline. If no *C. trachomatis* was detected, the study will end. If the detection of *C. trachomatis* is positive, patient will be asked to provide new self-collected vaginal and anorectal swabs for *C. trachomatis* detection (Fig. 1).

The research nurse will complete the e-CRF questionnaire about drug adherence. Participants will return the treatment box for a pill count as a proxy measure of drug adherence. Women will be asked whether they have experienced any diarrhea or vomiting that could affect the levels of antibiotic absorption, or any adverse events. Clinical data during the last 6 weeks (vaginal discharge, pelvic pain, abnormal bleeding, pain during sexual intercourse, anal discharge, anal itching, and tenesmus) and information about whether they have taken any other antibiotics will be collected.

Participants will complete a questionnaire about their sexual behavior during the last 6 weeks [sexual intercourse with a regular or occasional partner, nature of the intercourse (genital and/or anal and/or oral), and use of condoms] and their partner's treatment (Table 1).

At this stage, the study will end for all women with *C. trachomatis* negative vaginal and anorectal swabs and for those with a *C. trachomatis* positive vaginal swab (whatever the result of the anorectal swab) (Fig. 1). Women with a *C. trachomatis* positive vaginal swab will be informed by the practitioner at each center, who will provide treatment and information on the need for their partner(s) to be treated (usual recommendations).

Women with a *C. trachomatis* negative vaginal swab and a *C. trachomatis* positive anorectal swab will be asked to attend the participating center 4 months after treatment initiation (Fig. 1).

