#### Follow-up at four months

2.5.5

Participants will provide self-collected vaginal and anorectal swabs for *C. trachomatis* detection.

The research nurse will collect information on the e-CRF about other antibiotics taken and clinical data since the last visit (vaginal discharge, pelvic pain, abnormal bleeding, pain during sexual intercourse, anal discharge, anal itching, and tenesmus) (Table 1).

Participants will complete a questionnaire about their sexual behavior since the last follow-up visit [sexual intercourse with a regular or occasional partner, nature of the intercourse (genital and/or anal and/or oral), and use of condoms] and partner's treatment.

Data collected regarding participants will be anonymized.

If the participant does not attend the follow-up visit scheduled, the study site coordinator of each center will contact her by phone to schedule a new appointment within the 2 following weeks. To compensate participants for the time dedicated to the study, financial compensation will be given at the follow-up visits.

In the case where participants do not complete follow-up, attempts will be made to obtain information on the reasons for dropout. The last contact will be recorded.

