#### Secondary outcomes

2.6.2

We will estimate the prevalence of anorectal *C. trachomatis* infection concurrent with urogenital infection. The prevalence will be defined at the baseline by the number of women with an anorectal *C. trachomatis* infection divided by the total number of women included in the study.

For each participant, we will further determine the *C. trachomatis* genotype profile in order to identify whether the same *C. trachomatis* genotype profile is found in the vaginal-positive and anorectal-positive specimens.

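### The genotype match that scores autoinoculation cannot exclude same-strain partner reinfection, section 2.6.2 does not define the outcome, and the women who return at month 4 cannot support a comparison of arms

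*Protocol article*

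**What the plan says.** The Abstract (Methods and study design) gives one secondary outcome and its scoring rule: "The secondary outcome is autoinoculation from the rectum to the vagina, which will be evaluated based on the number of women with the same" genotype profile in a positive anorectal specimen at week 6 and a positive vaginal specimen at four months. The outcome serves the second half of the hypothesis at the end of the Introduction, that lower azithromycin efficacy in the rectum has a consequence, "resulting in reinfection by autoinoculation from the rectum to the vagina".

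Section 2.6.2 lists the secondary outcomes differently. The first is baseline prevalence of anorectal infection, with an explicit denominator ("divided by the total number of women included in the study"). The second is whether the same "genotype profile is found in the vaginal-positive and anorectal-positive specimens", with no time points. Autoinoculation is not named.

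Under section 2.5.4, women with a positive vaginal swab at week 6, and women negative at both sites, leave the study. Only a woman with a negative vaginal and a positive "anorectal swab will be asked to attend the participating center 4 months after treatment initiation".

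Partners are handled by giving information (2.5.1). Intercourse, condom use and partner treatment are recorded at week 6 (2.5.4) and again at month 4, in a "questionnaire about their sexual behavior since the last follow-up visit" (2.5.5). Section 2.5.7 types strains by *omp1* sequencing and then MLVA. The Discussion presents the ability to tell treatment failure from reinfection by these methods as a major strength.

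**The concern.** Typing tells whether two specimens hold the same strain. It does not tell how the strain reached the vagina. A regular partner who was not treated may carry the woman's own strain, and intercourse after week 6 can then produce the very match that the Abstract's rule calls autoinoculation. The data that would help to separate the two routes are collected, but they are not part of the stated rule.

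The comparison raises a second problem. The hypothesis is about a difference between treatments, but entry to the month-4 visit depends on the week-6 NAAT results, which treatment affects. If the proportion is taken among women who return, the randomized comparison is lost and one arm is nearly empty.

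At stake is the statement that rectal failure leads to vaginal reinfection. The primary comparison of anorectal cure does not depend on it.

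**Working it through.** **The two definitions side by side.** The Abstract gives the name autoinoculation, two sites, two time points and a rule (same profile). Section 2.6.2 gives two sites and concordance, but neither the name nor the time points. Under 2.6.2 alone, a baseline vaginal–anorectal match would also qualify, and that says nothing about later spread.

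**The plan's own figures (2.7.2).** Inputs: cure 99% (doxycycline) and 83% (azithromycin), 10% loss, two-sided 5%, power 90%.
- Compared rates: 0.99 × 0.90 = 0.891 and 0.83 × 0.90 = 0.747.
- The two-proportion formula with pooled variance and no continuity correction gives 149 per group (power 90.2% at 149).
- 149 / 0.65 = 229.2, rounded up to 230.

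Both stated sizes reproduce.

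**Who can return at month 4.** Women per arm = 230 × prevalence × 0.90 × (1 − cure rate). This is a ceiling: it treats every week-6 rectal positive as vaginal-negative and ignores later loss.

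| Prevalence | Azithromycin | Doxycycline | Total |
|---|---|---|---|
| 65% (planning) | 230 × 0.65 × 0.90 × 0.17 = 22.9 | 230 × 0.65 × 0.90 × 0.01 = 1.3 | 24.2 |
| 77.1% (pilot, 74/96) | 230 × 0.771 × 0.90 × 0.17 = 27.1 | 230 × 0.771 × 0.90 × 0.01 = 1.6 | 28.7 |

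**Denominator of returning women, about 23 versus 1.** The doxycycline proportion can only be 0/1 (exact 95% CI 0 to 97.5%) or 1/1 (2.5 to 100%). The smallest attainable Fisher p-value is 1/24 = 0.042, reached only if all 23 azithromycin women have one result and the single doxycycline woman the other.

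**Denominator of baseline dual-positive women, about 149 per arm.** The proportion is 0.90 × (1 − cure rate) × q, where q is the share of rectal failures that end in a match. The documents give no q, so a range is shown.

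| Assumed q | Azithromycin | Doxycycline | Fisher power, 149 per arm |
|---|---|---|---|
| 25% | 3.8% | 0.2% | 42% |
| 50% | 7.7% | 0.45% | 90% |
| 75% | 11.5% | 0.7% | 99% |

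This denominator keeps the arms as randomized, and the contrast can be read.

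**Effect of misclassification.** Let t be the true autoinoculation rate among returning women and r the rate of same-strain partner reinfection among the rest. The observed rate is t + (1 − t)r, and the false share is (1 − t)r divided by that. Neither rate is in the documents. For illustration, with t = 20%:
- r = 10%: observed 28%, false share 0.08/0.28 = 29%
- r = 20%: observed 36%, false share 0.16/0.36 = 44%
- r = 30%: observed 44%, false share 0.24/0.44 = 55%

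With about 24 women in all, each misclassified match moves the pooled proportion by 1/24 = 4.2 percentage points.

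**The case against.** Several stronger readings are tempting, and the article does not support them.

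- *The outcome is a count only, with no proportion and no split by arm.* Section 2.8 plans number, proportion and exact binomial interval for qualitative variables, overall and by treatment group. Only the choice of women for this denominator is open, and an article may leave that to the full protocol or the SAP.
- *The partner data will be ignored.* The article does not say so. One sentence in an abstract need not be the whole classification rule.
- *The count is biased upward overall.* Partner reinfection after week 6 can only add matches. But women already vaginal-positive at week 6 are dropped, which removes early partner reinfection and early autoinoculation alike, and losses at month 4 lower the count further. The net direction is not established.
- *The arms will be compared among returning women.* No between-arm test of autoinoculation is stated. The women are selected by NAAT result and do not select themselves.

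It is also fair that a denominator of all dual-positive women counts as non-events some women who were never swabbed at month 4, and that the trial's aim, power and treatment conclusions rest on anorectal cure.

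Three things remain: the Abstract and 2.6.2 disagree, the stated rule cannot tell the two routes apart, and the returning group is too small and too unequal for a comparison whatever the SAP adds.

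**Conclusion.** The point holds in this limited form. The Abstract and section 2.6.2 do not define the same secondary outcome. The Abstract's rule can count same-strain partner reinfection as autoinoculation, so the Discussion's claim that genotyping separates failure from reinfection holds for a new strain but not for a partner carrying the woman's own. At the planned rates at most about 23 azithromycin women and 1 doxycycline woman can return (27 and 2 at the pilot prevalence), so a proportion among them cannot compare treatments.

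The head counts rest on the plan's own cure, loss and prevalence figures and on the ceiling described above. The partner-reinfection and match rates are assumptions, shown as ranges. No stated number is wrong and the primary analysis is unaffected. The change should be made because the autoinoculation conclusion would otherwise claim more than the stated rule can show.

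**What to change.** 1. In section 2.6.2, name autoinoculation and define it as in the Abstract: the same *omp1*/MLVA profile in the week-6 anorectal and month-4 vaginal specimens.
2. Report matches separately by recorded intercourse, condom use and partner treatment since the week-6 visit. Call matches without unprotected exposure to an untreated partner *probable autoinoculation* and all others *indeterminate*. The window starts at week 6 because the vaginal swab was negative then.
3. Give each arm's number over all randomized women positive at both sites at baseline, descriptively with exact intervals. Beside it, show how many were eligible for month 4 and how many were swabbed, and note that women vaginal-positive at week 6 are not followed.
4. In the Discussion, limit the claim for genotyping: it identifies a new strain but not the route of an unchanged one.

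A table of week-6 vaginal positivity by arm is optional. The swab is already planned for dual-positive women who attend, but the result does not measure autoinoculation.

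The cost is outcome wording and one table, with no new visit or specimen. The drawbacks are fewer events classed as autoinoculation and reliance on self-reported exposure.

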**Discussion::**

The results of this trial will establish which treatment is more efficacious against anorectal infection and could affect recommendations for the treatment of urogenital *C. trachomatis* infection, taking into account concurrent anorectal infection.

**Trial registration numbers::**

EudraCT number: 2017-002595-15.

**ClinicalTrials.gov Identifier::**

NCT03532464. Date of registration: May 31, 2018.

**World Health Organisation International Clinical Trials Registry::**

NTC03532464. Secondary ID: CHUBX 2016/26. Date of registration: May 09, 2018.

## Introduction

1

*Chlamydia trachomatis* is the most commonly reported bacterial sexually transmitted infection (STI). Screening studies have found large differences depending on the population being tested, ranging from 1% to 3% in the general population to 10% to 15% in individuals consulting an STI screening center, or among women requesting an abortion.^[1–4]^ Up to 75% of *C. trachomatis* infected women are asymptomatic. If not treated, these infections can lead to complications and sequelae such as pelvic inflammatory disease, ectopic pregnancy, and tubal factor infertility.^[5]^ In addition to infection of the urogenital tract, *C. trachomatis* can also cause anorectal infections, which are typically asymptomatic.^[6]^ The proportion of women having a rectal *C. trachomatis* infection among those positive for urogenital *C. trachomatis* ranges from 45% to 100%.^[7–11]^ Notably, there is no reported association with anal intercourse.^[7–11]^ Recently, it has been suggested that the anal transmission of *C. trachomatis* in women may occur by autoinoculation from the vagina due to the close proximity of the vagina and the anus.^[8,12,13]^ Moreover, it has been suggested that women become infected with *C. trachomatis* orally through various sexual activities and that the organisms could establish a persistent infection in the lower gastrointestinal tract where the immune response is downregulated, suggesting the potential role of autoinoculation of cervical chlamydial infection from the rectal site.^[14,15]^ Such repeated urogenital infections could lead to reproductive tract morbidity.

For uncomplicated *C. trachomatis* urogenital infections, recommended treatments are azithromycin 1 g orally as a single dose or doxycycline 100 mg orally twice daily for 7 days.^[16,17]^ Single doses are most likely to be adhered to, whereas following a week-long regimen of daily antibiotics is likely to make people feel sick and thus defer sexual activities.^[18,19]^ A meta-analysis of 23 randomized controlled trials (RCTs) comparing both treatments found an overall efficacy of 94.3% for azithromycin and 97.4% for doxycycline on urogenital infections.^[18]^

Adequate treatment for anorectal *C. trachomatis* is currently under debate. A recent meta-analysis found a pooled treatment efficacy of 82.9% for a single 1 g dose of azithromycin and 99.6% for 100 mg of doxycycline twice daily for 7 days.^[20]^ While this suggests that doxycycline may be a more effective treatment, it must be emphasized that the quality of the evidence was poor, as the meta-analysis was based entirely on observational studies, with 75% (6/8) of the studies being retrospective case note reviews. If rectal *C. trachomatis* is a hidden reservoir influencing transmission rates and considering the potential complications of cervical infections, providing further evidence of the need for effective rectal treatments among women is highly relevant. These circumstances highlight the need for RCT evidence comparing azithromycin with doxycycline for the treatment of anorectal *C. trachomatis* in women. Our hypothesis is that the efficacy of azithromycin for anorectal *C. trachomatis* infection may be lower than that of doxycycline, resulting in reinfection by autoinoculation from the rectum to the vagina.

## Methods

2

### Aim

2.1

The principal aim of this trial is to compare the microbial cure obtained with a single 1 g dose of azithromycin versus 100 mg of doxycycline twice daily for 7 days for the treatment of anorectal *C. trachomatis* infection concurrent to a vaginal infection in women, 6 weeks after treatment initiation.

### Design

2.2

The Chlazidoxy trial is designed as a randomized, open-label, multicenter study comparing the efficacy (measured as the microbial cure) of a single 1 g dose of azithromycin versus 100 mg of doxycycline twice daily for 7 days for the treatment of concurrent anorectal and urogenital *C. trachomatis* infections. The trial will be conducted in accordance with the Declaration of Helsinki.

### Setting

2.3

Women will be recruited in France in primary care from 4 free STI screening centers “CeGIDD” (“Centre Gratuit d’Information, de Dépistage et de Diagnostic”) and from 3 pregnancy termination centers after they had an abortion. We chose these centers because of the high prevalence of urogenital *C. trachomatis* infections (10*–*12%)^[3,4,21]^ and because the French National Authority for Health recommends screening for vaginal *C. trachomatis* infection in these populations.^[3,21]^

### Patient characteristics

2.4

#### Inclusion criteria

2.4.1

(1)Female(2)Age ≥ 18 years(3)*C. trachomatis* positive nucleic acid amplification test (NAAT) for vaginal specimen at baseline(4)Women consulting STI screening centers with a negative β-hCG urinary assay and using efficacious contraception^[22]^(5)Women requesting an abortion at a pregnancy termination center and with efficacious contraception after abortion(6)Consultation in one of the participating centers(7)Agree to follow-up contact(8)Member or beneficiary of a social security system(9)Written informed consent signed by the participant and the investigator (no later than the inclusion day and before performing any examination required for the study)

#### Exclusion criteria

2.4.2

(1)Women with symptoms suggestive of pelvic inflammatory disease(2)Prescribed an antibiotic with antichlamydial activity within 21 days before screening or between screening and enrolment(3)Contraindications to tetracycline, macrolides, lincosamides, streptogramins, or ketolides (including allergy and treatment with colchicine, cisapride, ergot alkaloids, and retinoids)(4)Inability to swallow pills(5)Refusal to participate in the study(6)Objectives of the study not understood(7)Breastfeeding(8)Women with serious cardiac diseases: QT interval prolongation, cardiac arrhythmia, advanced heart failure (NYHA > III)(9)Women treated with anticoagulants or drugs with a definite potential of “*torsades de pointes”*(10)Women with severe liver diseases

A person enrolled in the trial will not simultaneously participate in another one.

### Context and procedure

2.5

#### Recruitment

2.5.1

Women with a *C. trachomatis* positive vaginal swab at the baseline will be approached by a research nurse and invited to take part in the trial (Fig. 1). The nurse will explain the trial and investigator will assess eligibility and obtain consent. Eligible women will be enrolled. Participants will provide a self-collected anorectal swab. Previous studies have found high feasibility and acceptability of self-collected anorectal testing in women who do not have an indication.^[10,11]^

**Figure 1 F1:**
[figure not shown]
Design of the Chlazidoxy study.

All women with urogenital *C. trachomatis* infection will be included without waiting for the NAAT result of the anorectal specimen because treatment cannot be delayed. However, the study population will consist of only women with both *C. trachomatis* positive vaginal and anorectal swabs.

Information on the need for partner(s) to be treated will be provided. Sexual abstinence or protected intercourse with the partner(s) up to 7 days after the single dose of azithromycin or after 7 days of doxycycline will be recommended (usual recommendations).

The research nurse will complete an electronic Case Report Form (e-CRF) at the time of recruitment of the demographic characteristics (birth date, country of birth, marital status, education level, professional status), and biological (previous *C. trachomatis* infection, HIV-serology, *Neisseria gonorrhoeae* infection, hepatitis B virus, and syphilis serology) and clinical data (vaginal discharge, pelvic pain, abnormal bleeding, pain during sexual intercourse, anal discharge, anal itching, tenesmus). Participants will complete a questionnaire about their sexual behavior [regular sexual partner(s), occasional sexual partner(s) in the last 12 months, use of condoms, anal and oral intercourse] (Table 1).

